### Corpus

The clinical information corpus used is the TREC 2014 and 2015 document collection [37,60]. This consists of a snapshot of the Open Access Subset of PubMed Central taken on January 21, 2014. It contains a total of 733,138 articles. The corpus was preprocessed according to the method employed by [61], including the removal of all HTML/XML tags, all numbers and all nonalphabetical characters. The corpus was then indexed with Galago (the Lemur Project) [62] version 3.12 using a Porter stemmer and stop words removal. After indexing, all very rare terms were also removed, that is, all terms with 3 or less occurrences in the corpus.

### Custom Search System

A custom search engine and interface, together called Taskiir, is employed for the evidence search process (see Figure 2). Similar to normal commercial search engines, Taskiir allows the participant to write their query and perform a best match search of documents in the corpus. A snippet, highlighting matching query terms, is then provided in the SERP, which shows up below the query. Users can then select documents of interest to view the full text. While viewing the full text document, the participant can also select (with their mouse) any text or graphics that they want to use as evidence for their final answer. The participant can view their evidence or complete the task at any time. Instructions on using the system are provided on each page, and a mandatory walk-through tutorial is provided before starting the study.

To investigate the impact of search system effectiveness on clinical decision making (RQ2), Taskiir utilizes 2 search algorithms: (1) A state-of-the-art system, which is an improved version of the TREC 2015 CDS Task A winning system [61]. The TREC 2015 CDS track was targeted to identify the state-of-the-art IR system because the topics in Task A were of a similar clinical nature to the Westbrook tasks and the search corpus was the same as that used in this study. The 2 improvements made over the winning system include the removal of negated Unified Medical Language System (UMLS) terms from the UMLS query expansion terms as well as a change to the pseudorelevance feedback term weighting (from 0.75 to 0.5). All improvements resulted from tuning parameters on the CDS 2014 test collection and testing on the 2015 collection to avoid data overfitting. (2) A baseline document retrieval system consisting of a BM25 algorithm, which is a widely adopted best-match retrieval method. It is the default, out-of-the-box method employed by many search engines, including the very popular Elasticsearch (Elasticsearch BV) [63] and Lucene (Apache) systems [64]. The parameters were set to default values (K=1.2; b=0.75).

### Information Retrieval Evaluation Measures

Document retrieval performance figures for both systems are shown in Table 3. The measures depicted were the standard set chosen for the TREC 2014 and 2015 CDS task. IR system performance measures are usually calculated for a ranked retrieval of 1000 documents MAP, for example, is the average of all precision values taken at each rank where a relevant document is found. Precision at a given rank is the number of relevant documents found up to that rank divided by the rank. MAP is useful because it provides a single measurement of system performance across all queries. However, because MAP is only averaged across relevant rank positions, results can be biased toward a system retrieving fewer relevant documents but at lower rank positions. Precision at rank position 10 is simply the precision calculated at rank position 10. It is useful to identify high-precision systems that provide many relevant documents in the first 10 documents retrieved. This is often pertinent to a clinical search where clinicians have little time to view many documents. R-precision (R-prec) is the ratio r/R where r is the number of relevant documents retrieved by the system up to ranking R and R is the number of judged relevant documents for that query. Unlike MAP, R-prec takes into consideration the number of relevant documents that could be found and, therefore, is helpful for search tasks where recall is important. R-prec is a useful measure for systems that need to return many or all of the relevant documents, for example, in clinical cases that require physicians to seek alternatives, say for treatments. Discounted cumulative gain (DCG) sums the gain at each rank position (ie, the relevance grading value) multiplied by a discount factor that takes into consideration that lower ranked documents are less likely to be read. Normalized discounted cumulative gain (nDCG) compares the DCG with an ideal DCG for each rank, so that scores are normalized between 0 and 1. nDCG is designed to promote systems that provide more relevant documents higher up in the ranking.

One problem with all these standard measures is the underlying assumption that all relevant documents within the test collection are identified for each query. This is rarely the case because of cost limitations. In the measures above, unjudged documents are considered as nonrelevant; however, this may not be the case. To account for unjudged documents, Aslam et al derived 2 new measures, inferred nDCG and inferred average precision, which have become accepted methods of evaluating system retrieval performance when relevance judgements are incomplete [65].

### Sample Size

The 2 largest and most similar studies [16,18], both commenced with a presearch correct answer rate of around 30% (29% and 32%) and a postsearch rate around 50% (50% and 46%). Using this as our basis, we wanted to be able to discriminate between the postsearch correct answer rate between each of the 3 time-constrained cohorts. Therefore, to derive the sample size, we estimated that the correct answer rates might vary evenly by 10 percentage points between each group, starting at no improvement. This creates 3 datasets with average correct answer rates of 30%, 40%, and 50% for the 3-, 6- and 9-min cohorts, respectively. Applying a 2-proportion statistical comparison (ie, a 2-sample, 2-sided equality) [66], between each pair of answer rates and setting statistical power to 90%, error rate to 5%, and equal sample sizes per cohort, the minimum sample size required is 514 per cohort, which equates to 32 people per cohort sitting 16 tasks or 96 people in total.

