#### After Initial Login

The participant is asked 7 questions to capture demographic data, search, and medical experience (see Multimedia Appendix 1) as well as sleep information. A 5- to 10-min video tutorial follows where the study is described in more detail and the participant is shown how to use the SML search engine. The tutorial emphasizes that the participant must answer the question without the aid of other people or by looking at other resources. Once complete, the participant is shown specific instructions (provided in Multimedia Appendix 2 that again reinforce the participant’s obligation to perform the test alone, before they are permitted to move onto the 2-stage assessment.

#### In Stage 1

A total of 16 clinical tasks are presented to the participant, one at a time. To complete each task, the clinician must answer a single question within a few minutes, although this time limit is not enforced. In addition, 14 of the 16 tasks require the participant to select 1 of 4 answers (yes, no, conflicting evidence, and do not know) and the other tasks require a 1- to 2-word answer. At the end of the last task, the system will move the participant to stage 2 of the study.

#### In Stage 2

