### Statistical Analyses

To assess the impact of introducing the SML search system on clinical decision quality (RQ-1), each participant’s answer, both presearch and postsearch, will be coded to right (R) or wrong by comparing the participant’s answer with an expert judged assessment (gold answer) of each task. Samples for which (1) no evidence is captured and (2) no relevant documents are marked (either as essential or helpful), by the participant for their postsearch answer, will be discarded, as the value of the search system cannot be confirmed in these cases. Therefore, the decision quality is defined by the correct answer rate (number of right answers/total sample count (N)). A further detailed analysis will be performed of the collected evidence to identify tasks where the literature may contradict the gold answers. Where this occurs, the task answers will be reviewed by experts and overall correct rates adjusted.

To assess the significance of any change in the proportion of right or wrong answers, the McNemar test will be employed because it is a nonparametric test suited to a binary result, with samples taken at 2 points in time. Nonparametric is a better model to assume, given that the data distribution is unlikely to be regular because of the different medical groupings of participants. The sign test, which is also a nonparametric test, will be used to identify any significant changes to the correct rate. To assess any differences between the participant groups (nurses, doctors, and students), a Chi-square analysis will be performed. The participant’s confidence in their answers will be assessed presearch and postsearch to identify any significant changes relating to search intervention, also using chi-square analysis.

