To assess the impact of search engine performance on clinical decision quality (RQ-3), a similar set of analyses will be performed as that for RQ-1, except broken down by search system (state-of-the-art and BM25). In addition, the same ANOVA methods employed for time-constraint categories in RQ-2 analysis will be performed. In addition, an ANOVA will be performed across system categories and system time constraints to identify cases where system performance effects may matter most. The impact of search engine performance on clinical decision time (RQ-3) will also be assessed by evaluating the postsearch task completion times for those tasks that were completed (ie, relevant documents and/or evidence identified). This is measured in 2 ways: (1) search time only and (2) search time plus time spent filling in the answer form. Differences in search times between the systems will be assessed using the chi-square analysis. Finally, a participant-derived performance assessment of the 2 systems can be constructed by building a graded query relevance (QREL) listing (standard format for representing relevance assessments in IR), by query, based on all participants’ relevance ratings. Using this QREL, a recomparison of the 2 systems can be evaluated and compared using the formal TREC evaluation results to provide better insight into any changes observed (or not) in the clinical decision and timing results for the 2 systems.

There are a number of potentially confounding factors within the experimentation. A covariant analysis (repeated measure ANOVA) will be performed on the task number, task at total duration point (for fatigue), and time transitions (eg, 3-min task to 6-min task and 3-min task to 9-min task).

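### The between-limit and between-system comparisons of postsearch correctness do not adjust for the presearch answer already collected; this costs some precision but causes no bias

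*Protocol article*

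**What the plan says.** In stage 1 (Procedures, In Stage 1), "A total of 16 clinical tasks are presented to the participant, one at a time", to be answered unaided. Stage 2 repeats the same tasks in the same order, now with a time limit and a search system. Under Statistical Analyses, "each participant’s answer, both presearch and postsearch, will be coded to right (R) or wrong". There is therefore a binary baseline of the outcome for each participant and task, recorded before either experimental factor is applied.

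The Sample Size section fixes the target contrast: "we wanted to be able to discriminate between the postsearch correct answer rate between each of the 3 time-constrained cohorts". It assumes "average correct answer rates of 30%, 40%, and 50% for the 3-, 6- and 9-min cohorts, respectively" and applies a two-sample, two-sided comparison of proportions, "setting statistical power to 90%, error rate to 5%, and equal sample sizes per cohort". It cites a presearch rate of about 30% from two earlier studies, but only as the starting point for the assumed rates. No presearch term enters the calculation.

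Statistical Analyses pairs the presearch and postsearch answers with McNemar and sign tests for RQ-1, then repeats those analyses by time limit (RQ-2) and by search system (RQ-3). On covariates it says: "A covariant analysis (repeated measure ANOVA) will be performed on the task number, task at total duration point (for fatigue), and time transitions". The presearch answer is not in that list. RQ-3 also plans an ANOVA across systems and limits, again with no mention of the presearch answer.

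**The concern.** Whether a participant already knew the answer to a question is likely to predict whether the postsearch answer is right. A between-limit or between-system comparison that leaves this out carries variance that the trial could remove with data in hand. It also leaves any chance difference in prior knowledge between the compared sets of answers uncorrected in the point estimate.

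The paired tests do not fill the gap. McNemar or sign tests run separately at 3, 6 and 9 min show whether answers changed within each limit. A significant change at one limit and a non-significant one at another is not a test of the difference between limits. The same holds for the two systems.

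Participant and task terms do not fill it completely either. They capture how able a person is and how hard a question is, but not whether this person knew this answer. What is at stake is precision in the contrasts that answer RQ2 and RQ3.

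**Working it through.** **Inputs from the article.** Postsearch rates 30%, 40% and 50%; two-sided 5%; 90% power; equal groups; 514 answers per limit stated, and 32 x 16 = 512 planned; presearch rate about 30%. **Not in the article, so assumed:** the presearch-postsearch correlation ρ, taken from 0.1 to 0.6.

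**1. The plan's own figure.** The hardest pair is 40% v 50%. Unpooled formula: n = (1.960 + 1.282)² x (0.24 + 0.25) / 0.10² = 514.9 per limit, which matches the stated 514 (the pooled form gives 519). With 512 answers, 0.10 / √(0.49/512) = 3.23, and 3.23 - 1.96 = 1.27, so power is 89.8%. The stated power stands on its own terms.

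**2. Adjusting for the presearch answer.** The variance is multiplied by (1 - ρ²). Answers are treated as independent, as in the plan.

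| Assumed ρ | Variance factor | n per limit for 90% | Power with 512 |
|---|---|---|---|
| none | 1.00 | 515 | 89.8% |
| 0.1 | 0.99 | 510 | 90.1% |
| 0.2 | 0.96 | 495 | 91.0% |
| 0.3 | 0.91 | 469 | 92.3% |
| 0.4 | 0.84 | 433 | 94.1% |
| 0.5 | 0.75 | 387 | 96.2% |
| 0.6 | 0.64 | 330 | 98.1% |

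With a 30% presearch rate, the largest attainable correlation is 0.80 against a 40% postsearch rate and 0.65 against 50%, so 0.6 is close to the ceiling.

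**3. The same in terms of retained answers.** Simulation (20,000 runs, 512 independent answers per limit) of a risk difference standardised over presearch right/wrong:

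| Presearch-correct answers still correct | ρ at 40% / 50% postsearch | Power, unadjusted to adjusted |
|---|---|---|
| 60% | 0.27 / 0.13 | 89% to 91% |
| 70% | 0.40 / 0.26 | 89% to 93% |
| 80% | 0.54 / 0.39 | 89% to 95% |
| 90% | 0.67 / 0.52 | 89% to 98% |

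**4. Gain over participant and task terms.** Steps 2 and 3 credit the covariate with variance that participant and task terms would partly remove. A simulation of the 96 x 16 design, with limits rotated over three cohorts and those terms in the model, had overall correlations of 0.34, 0.47 and 0.59. Adding the presearch answer moved power from 93% to 95%, 92% to 97% and 93% to 98%. With no person-by-task knowledge effect, power was 95% either way. A separate simulation of the same design gave gains of about 0 to 3 points. The range to quote is 0 to 5 points.

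**5. Chance imbalance.** If answers are independent, the presearch rate differs between two limits with SE √(2 x 0.21/512) = 2.9 points. A 1-SE imbalance moves the postsearch difference by ρ x √(0.25/0.21) x 2.9, which is about 0.9 points at ρ = 0.3 and 1.6 points at ρ = 0.5, against a target difference of 10 points.

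**6. A change score is not a substitute.** Its variance in each group is 0.21 + p(1-p) - 2ρ√(0.21·p(1-p)). For 40% v 50% this needs 671 answers per limit at ρ = 0.3, 575 at 0.4 and 480 at 0.5. It beats the unadjusted test only when ρ exceeds 0.42 / [2 x (0.2245 + 0.2291)] = 0.46.

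**The case against.** The strongest reply is that this is an efficiency option and that nothing in the plan is wrong. Participants are randomised to timing cohorts, and limits and systems rotate over tasks, so leaving out a baseline covariate does not bias the contrasts. Sizing on an unadjusted test is conservative if adjustment is used later. All of that stands. A reader might infer that the time-limit effect would be biased or that the 90% power is wrong. The documents support neither.

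It can also be said that the presearch answer is not ignored, since the paired tests use it. That is correct, but those tests compare times within a category and not the categories themselves.

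The size is open to attack as well, and rightly. A reader might take the step from 89.8% to 96.2% as the expected benefit. That figure needs an assumed correlation of 0.5 and a comparator with no participant or task terms. Tasks were chosen to have answers that are not obvious, and 14 of 16 offer four options, so some correct presearch answers may be guesses. That would lower the correlation.

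The imbalance argument is weak too. Every task is done equally often under each limit, and each participant works under all three. Part of the imbalance is thus controlled by design, the 2.9-point SE is approximate, and what remains is already covered by the test's error rate.

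The covariate list might be thought a matter for a fuller analysis plan. The article does, however, name both the test it sizes on and the covariates it will analyse, and this baseline appears in neither place. The chi-square sentence under RQ-2 follows the time-out analysis and may cover time-outs only. On either reading, no between-limit test of correctness that uses the presearch answer is described.

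**Conclusion.** The point holds as a modest, nearly free improvement. The between-limit and between-system comparisons of postsearch correctness make no use of a baseline recorded for the same person and question. Against the plan's unadjusted test, with independent answers, power for 40% v 50% would rise from 89.8% to about 90-98% for correlations of 0.1 to 0.6. Against a model that already has participant and task terms, the gain is about 0 to 5 points, and it is nil if prior knowledge has no person-by-task component. These figures rest on a correlation that the article does not give, and those in steps 2, 3 and 5 ignore clustering by participant and task, which is a separate matter. The article sets no power target for the system comparison, so no size is claimed there.

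**What to change.** For RQ2 and RQ3, analyse postsearch correctness in one model, for example a logistic mixed model or GEE. Enter time limit and search system as factors, participant and task as terms, and the presearch answer to the same question (right/wrong) as a prespecified covariate. Add that answer to the covariates named under Statistical Analyses.

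Report standardised (marginal) risk differences between limits and between systems, so that results stay on the scale of the raw correct rates and remain comparable with the earlier studies. Keep the raw rates as description and the McNemar and sign tests for the before/after question. Do not use a change score for the between-category contrasts.

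The cost is one covariate and a sentence or two in the analysis section. No new data, participants or procedures are needed, and the sample size calculation can stand. The choice should be recorded before the outcome data are analysed.

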**Figure 2 figure2:**
[figure not shown]
Screenshot of the Taskiir custom search system interface. Shows the task in the top left, search query box in the top right, and search results below.

**Table 3 table3:** Comparison of document retrieval performance figures, across the text retrieval conference (TREC) 2015 test collection, for systems used in this study and the winning TREC 2015 system.

System	Inferred normalized discounted cumulative gain	Inferred average precision	Precision at rank position 10	R-precision	Mean average precision
Wayne State University (WSU) system^a^	0.2928	0.0777	0.4633	0.2329	0.1851
State-of-the-art system	0.3159	0.0849	0.4800	0.2401	0.1930
BM25 system	0.2168	0.0461	0.3600	0.1717	0.1114
State-of-the-art versus BM25 (%)	+46^b^ (*P*=1.2E-05)	+84^b^ (*P*=0.0056)	+33^b^ (*P*=4.1E-04)	+40^b^ (*P*=4.3E-05)	+73^b^ (*P*=7.9E-05)

^a^As per TREC 2015 CDS, task A, automatic runs listed in [37] for task summary.

^b^Significance using paired *t* test

### Task Order, System Rotation, and Task Timing

Task order and system rotation is set as per the table in Multimedia Appendix 4 for each participant to minimize confounding factors. The design is as follows:

A Latin square experimental design is constructed for 16 tasks and 16 participants to minimize the impact of user fatigue on specific tasks.To minimize task order effects, each column of the square is randomized.To incorporate a within-subject design across the system variable, 2 sets of the Latin square derived in (2) are required with alternating use of systems. The first tranche of 16 participants will start their first task with the state-of-the-art system, whereas the second tranche will start with BM25 system. In this way, across the 32 participants, each system will be used equally across all tasks and will experience the same task-order pattern.

The search time allowed for each task is controlled by applying a time limit for each task the participant performs. Participants are randomly assigned to 1 of 3 timing cohorts. The time constraint by task number is specified for each cohort in Multimedia Appendix 5. The rotation of task timing ensures that:

the maximum duration for search in stage 2 is fixed to 96 min for all participantseach task is conducted under all time constraints an equal number of times (32 per cohort)a within-subject design across the time constraint variable such that each participant performs 4 to 6 tasks per time constrainttask time constraints are applied in the same random order according to the task order rotation Latin square, specified above

### Statistical Analyses

To assess the impact of introducing the SML search system on clinical decision quality (RQ-1), each participant’s answer, both presearch and postsearch, will be coded to right (R) or wrong by comparing the participant’s answer with an expert judged assessment (gold answer) of each task. Samples for which (1) no evidence is captured and (2) no relevant documents are marked (either as essential or helpful), by the participant for their postsearch answer, will be discarded, as the value of the search system cannot be confirmed in these cases. Therefore, the decision quality is defined by the correct answer rate (number of right answers/total sample count (N)). A further detailed analysis will be performed of the collected evidence to identify tasks where the literature may contradict the gold answers. Where this occurs, the task answers will be reviewed by experts and overall correct rates adjusted.

To assess the significance of any change in the proportion of right or wrong answers, the McNemar test will be employed because it is a nonparametric test suited to a binary result, with samples taken at 2 points in time. Nonparametric is a better model to assume, given that the data distribution is unlikely to be regular because of the different medical groupings of participants. The sign test, which is also a nonparametric test, will be used to identify any significant changes to the correct rate. To assess any differences between the participant groups (nurses, doctors, and students), a Chi-square analysis will be performed. The participant’s confidence in their answers will be assessed presearch and postsearch to identify any significant changes relating to search intervention, also using chi-square analysis.

To assess the impact of time constraints on clinical decision quality (RQ-2), the analyses above will be repeated with a breakdown by time constraint category, that is, 3, 6 and 9 min. In addition, an analysis of time-outs by constraint category will be conducted to assess the impact of time constraints on task completion. Time-outs are defined as samples where at the postsearch answer stage (1) the task timer reaches the constraint duration and (2) the participant provides no evidence to support their answer. It is assumed that in a time-out scenario, the participant was unable to complete the task. Significant differences by time-constraint category will be analyzed using the chi-square analysis. An analysis of variance (ANOVA) will be performed across confidence, difficulty, participant-perceived time impact assessments (impact of time on answer, evidence capture, and stress), and search behaviors, such as SERP dwell time, number of queries issued, number of documents opened, and the quantity of evidence items selected. To gain an understanding of the impact of providing a time constraint on the decision-making process, both the average time to search and the average proportion of available search time used will be evaluated and compared for the different task-timing samples. Tombros et al [67] used this proportional figure as a further gauge of participant stress and it can be compared with the reported stress by the participants.

To assess the impact of search engine performance on clinical decision quality (RQ-3), a similar set of analyses will be performed as that for RQ-1, except broken down by search system (state-of-the-art and BM25). In addition, the same ANOVA methods employed for time-constraint categories in RQ-2 analysis will be performed. In addition, an ANOVA will be performed across system categories and system time constraints to identify cases where system performance effects may matter most. The impact of search engine performance on clinical decision time (RQ-3) will also be assessed by evaluating the postsearch task completion times for those tasks that were completed (ie, relevant documents and/or evidence identified). This is measured in 2 ways: (1) search time only and (2) search time plus time spent filling in the answer form. Differences in search times between the systems will be assessed using the chi-square analysis. Finally, a participant-derived performance assessment of the 2 systems can be constructed by building a graded query relevance (QREL) listing (standard format for representing relevance assessments in IR), by query, based on all participants’ relevance ratings. Using this QREL, a recomparison of the 2 systems can be evaluated and compared using the formal TREC evaluation results to provide better insight into any changes observed (or not) in the clinical decision and timing results for the 2 systems.

There are a number of potentially confounding factors within the experimentation. A covariant analysis (repeated measure ANOVA) will be performed on the task number, task at total duration point (for fatigue), and time transitions (eg, 3-min task to 6-min task and 3-min task to 9-min task).

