The participant must complete the same 16 tasks in the same order as stage 1; however, the participant must now use Taskiir to help them answer the question and to find evidence to support their answer. Evidence is collected by the participant selecting text, images, or both from the source documents they read. The time allocated to search for each task is set according to the timing cohort the participant belongs to and will be one of 3, 6, or 9 min. The participant is told of the time allocation at the start of each question and a minute-by-minute countdown timer is always visible to the participant; warnings are given 30 seconds before time-out. At time-out, the screen is blocked, and the participant is taken to the task completion screen to enter their final details. Other methods of communicating the time limit were trialed during development of the system. In the end, the above method was chosen because it provided a balance between (1) making the participant aware of the time allocated for each question, (2) avoiding time anchoring (where the participant incorrectly assumed all questions are allocated the same time as the first question), (3) keeping them updated with the time remaining so they do not run out of time without warning, and (4) not distracting the participant with time information (eg, using a second-by-second countdown timer that diverted too much attention away from the task).

As this is the first such study measuring the impact of time variation, a few time limits covering a wide range are required to generate significant differences in the outcomes. A useful starting point to establish these time limits is the average completion time of 6.1 min per question, reported in the Westbrook study [33]. From the same study, the SD, based on the average completion times for each of the 8 questions, across 2 systems, is 3.1 min. Therefore, time limits are set at the average question answer time (6 min) and approximately 1 SD either side of this (3 and 9 min). These limits should induce time pressures for 84% of questions with a 3-min time limit, 50% of questions with a 6-min time limit, and 16% of questions with a 9-min time limit. From previous studies, realistic answer timeframes for busy clinicians should be below 5 min [3,15,35], so the 3 proposed time limit cohorts will encompass this pragmatic indicator of search time suitability.

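### The correct answer rate excludes stage-2 answers with no evidence and no relevant rating, so time limits and search systems are compared on subsets selected after assignment

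*Protocol article*

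**What the plan says.** Under Statistical Analyses (RQ-1), the rule covers "Samples for which (1) no evidence is captured and (2) no relevant documents are marked (either as essential or helpful"; the sentence then goes on: "by the participant for their postsearch answer, will be discarded, as the value of the search system cannot be confirmed in these cases". Decision quality is then defined, as a consequence, as right answers over the total sample count. I read that count as what remains after discarding.

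For RQ2, "the analyses above will be repeated with a breakdown by time constraint category". For RQ3, "a similar set of analyses will be performed as that for RQ-1, except broken down by search system". A separate RQ2 analysis counts time-outs, meaning tasks where the timer reached the limit and no evidence was given: "It is assumed that in a time-out scenario, the participant was unable to complete the task". No analysis of all samples is described.

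Three other places matter:

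- Procedures (In Stage 2) says that at time-out the participant is moved to the completion screen, and Table 1 lists the answer as a postsearch item.
- The same subsection expects unequal pressure: "These limits should induce time pressures for 84% of questions with a 3-min time limit, 50% of questions with a 6-min time limit", and 16% at 9 min.
- Task Order, System Rotation, and Task Timing builds a rotation in which each task is done equally often under each limit and with each system.

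**The concern.** Capturing evidence and rating a document are things the participant does during the search. Less time leaves less opportunity for either, and a weaker ranking offers fewer documents worth rating. The filter is therefore a possible consequence of the two factors under test. Comparing correct answer rates among samples that pass it is not a comparison of the limits or systems as assigned, and it gives up the balance the rotation was built to secure.

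The outcome is not missing for these samples, because an answer is still entered. The rule deletes observed results. The time-out count reports some of them but does not return them to the correct answer rate.

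The stated reason, that the system's value cannot be confirmed, also fits poorly with RQ2 and RQ3. A search that yields nothing usable says something about the limit or the system. For RQ1 the rate describes only samples with recorded evidence or a relevant rating, not the effect of making the system available.

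**Working it through.** **1. Which samples go.** I read the rule as requiring both conditions. The RQ3 time analysis supports this, since it treats a task as completed when relevant documents, evidence or both were identified. Combined with the time-out definition:

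- time-out with no document marked essential or helpful: discarded
- time-out with at least one such document: kept
- no time-out, but no evidence and no such document: discarded

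**2. The plan's own figure.** Sample Size uses 30%, 40% and 50% correct at 3, 6 and 9 min, with 90% power and a two-sided 5% error rate. For 40% vs 50%, unpooled:

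(0.24 + 0.25) × (1.960 + 1.282)² / 0.10² = 514.9, which agrees with the stated 514.

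The design supplies 32 × 16 = 512 per limit, with power of 89.7%. There is no allowance for discards. From loss of answers alone, power for this pair would be 88.1%, 86.4%, 82.2% and 76.9% at 5%, 10%, 20% and 30% discarded.

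**3. Effect on RQ2.** Let T be the all-sample rate, d the share discarded and q the share of discarded answers that are right.

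kept rate = (T − d·q) / (1 − d), so kept rate − T = d(T − q) / (1 − d)

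The shift is upward where q is below T and downward where q is above T. The documents give neither d nor q, so both are assumed. Take T = 30/40/50% and let d be a fraction f of the time-pressured shares 84/50/16%:

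- f = 25%: d = 21%, 12.5%, 4%
- f = 50%: d = 42%, 25%, 8%

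| f | q | kept at 3 / 6 / 9 min | 9 vs 3 min | power, 6 vs 9 min |
|---|---|---|---|---|
| none discarded | – | 30.0 / 40.0 / 50.0% | 20.0 points | 89.7% |
| 25% | 10% | 35.3 / 44.3 / 51.7% | 16.4 points | 62% |
| 50% | 10% | 44.5 / 50.0 / 53.5% | 9.0 points | 17% |
| 25% | 40% | 27.3 / 40.0 / 50.4% | 23.1 points | 89% |
| 50% | 40% | 22.8 / 40.0 / 50.9% | 28.1 points | 89% |

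For example, at f = 25%, q = 10% and 3 min: (0.30 − 0.21 × 0.10) / 0.79 = 0.353. The power figures treat answers as independent, as the plan's calculation does.

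**4. Small discard shares.** Suppose 10% of 3-min and 2% of 9-min samples are discarded, with kept answers 50% right at both limits and discarded answers 30% right. The all-sample rates are 0.90 × 50 + 0.10 × 30 = 48.0% and 0.98 × 50 + 0.02 × 30 = 49.6%. The planned analysis would show 0 where the all-sample difference is 1.6 points.

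**5. Effect on RQ3.** Assume all-sample rates of 45% (state-of-the-art) and 40% (BM25).

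- Discards 10% and 20%, q = 10%: 0.44/0.90 − 0.38/0.80 = 48.9% − 47.5% = 1.4 points
- Discards 10% and 20%, q = 40%: 0.41/0.90 − 0.32/0.80 = 45.6% − 40.0% = 5.6 points
- Discards 10% and 30%, q = 10%: 0.44/0.90 − 0.37/0.70 = 48.9% − 52.9% = −4.0 points

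The same 5-point difference can shrink, grow or reverse.

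**6. Effect on RQ1.** Assume 30% correct before and 50% after search, and that discarded pairs show no change. The gain among kept pairs is 20/(1 − d): 21.1, 22.2, 25.0 and 28.6 points at 5%, 10%, 20% and 30% discarded.

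**The case against.** The rule has a rationale. Participants work unsupervised online and are required to use the search system, so limiting RQ1 to confirmed use answers a recognisable question. That stands as a reason to keep it as a secondary analysis. It is weaker for RQ2 and RQ3, where the filter may itself respond to the factor compared. Data Capture also logs queries and opened documents, so non-use could be identified without selecting on a productive search.

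There are partial safeguards. Time-outs and the number of evidence items are compared by limit, the ANOVAs are repeated by system, and task-level data will be released. For RQ1, discarded pairs with no pre/post change would not enter the McNemar statistic, so the rates are affected more than that test. All of this stands, but none of it restores the discarded answers to the correct answer rate. The wording for RQ3 is a similar set of analyses, so carry-over there is the natural reading rather than an explicit statement.

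A reader might infer more than the documents support:

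- *That the rule hides the effect of time pressure or of the weaker system.* This needs discarded answers to be mostly wrong. Some may come from participants who already knew the answer and collected nothing, and the contrast can then widen.
- *That most time-outs leave the denominator.* The share of time-outs with no relevant rating is not given.
- *That only successful searches are kept.* One evidence item or one helpful rating retains a sample, whether or not its answer is right.
- *That 84% vs 16% are discard rates.* They are expected shares of questions under time pressure, derived from completion times in an earlier study. They serve above only as a scale for assumptions.

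On assignment, timing cohort is randomised, whereas system alternates within a Latin square. The point does not depend on that difference.

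**Conclusion.** The concern holds as a selection problem of unknown size and sign. The plan conditions its main outcome on events that follow assignment and plausibly depend on it, carries that into the RQ2 and RQ3 comparisons, and describes no all-sample analysis alongside.

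Under the assumptions shown, the planned 20-point contrast between 9 and 3 min could appear as anything from 9.0 to 28.1 points, and an assumed 5-point system difference as anything from −4.0 to 5.6 points. If discards are few, the distortion may be under 2 points. For RQ1, inflation follows only if discarded pairs show no gain, or less gain than the kept pairs. The change is worth making because the direction could not be known in advance and every main comparison is exposed.

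**What to change.** Make the primary analysis for all three research questions every stage-2 task with its entered answer, analysed by the time limit and system assigned. Score a blank or *do not know* as not correct, unless it is the gold answer. Keep the discard rule as a secondary analysis labelled as confirmed use, and report the number discarded by time limit and by system so that readers can judge the selection.

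This changes analysis wording only, since the answers are already collected. It keeps 96 × 16 = 1536 pre/post pairs, or 512 per limit, and so preserves the planned power of about 90%. The small cost is that the RQ1 estimate becomes the effect of offering the system and may look less favourable.
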